#### Stage 2 – Efficacy trial

##### Primary outcome

Proportion of participants with severe diarrhoea within 3 weeks of HSCT (severe diarrhoea defined as: 3 consecutive days of Bristol Stool Chart (BSC) 6 + at a frequency of 4 + bowel movements/day above baseline).

##### Secondary outcomes

Mean duration of BSC 6 + within 3 weeks of HSCT.Mean BSC score within 3 weeks of HSCT.Mean stool frequency with 3 weeks of HSCT.Change in body weight (kg).Incidence of FMT treatment-emergent adverse events.Proportion of participants that complete full course (as indicator of adherence).Incidence of fever (collected from clinical notes).Incidence of blood stream infections (defined as positive blood culture, collected from clinical notes).Use of supportive care interventions:
Empirical antibiotic use (type, dose and duration, collected from clinical notes).Total parenteral nutrition (incidence and duration, collected from clinical notes).Loperamide (incidence, dose and duration, collected from clinical notes).Opioid analgesics (incidence, dose and duration, collected from clinical notes).Other relevant medications used to control symptoms.
Duration of hospitalisation (days).Symptom burden (defined using ESAS-r-CS).

##### Exploratory outcomes

Gut microbiota composition assessed using microbial genomic sequencing performed on longitudinal stool samples.Plasma short chain fatty acid concentrations assessed in longitudinal blood samples.Plasma citrulline (biomarker of mucosal barrier injury) assessed in longitudinal blood samples.Salivayr metabolome and microbiome.

Safety and adherence will continue to be assessed as per Stage 1.

See Table 3 for study assessment schedule.

**Table 3 Tab3:** Study assessment schedule

Assessment	Before prophylactic FMT	After prophylactic FMT	Day of HSCT (day 0)	During in-patient stay	Before recovery FMT	After recovery FMT	Day + 21	1 month after
Patient demographics								
Comorbidities								
Medications								
Diagnosis/treatment details								
ECOG performance status								
Adherence								
Bristol stool chart (BSC)			Daily					
Frequency			Daily					
Body weight				2-3x weekly while an in-patient				
Symptom burden			*	*	*	*		*
Adverse events ^								

### Biospecimen collection

Stage 1: Faeces will be collected before and after FMT to confirm engraftment in the safety run in cohort..

Stage 2: Blood, saliva and stool (faeces) will be collected from participants longitudinally throughout the study. A maximum of 2 × 9 ml EDTA blood tubes and 2 × 9 ml SERUM (clotting) blood tubes will be collected at each timepoint. Saliva will be collected using ORAGENE-DNA OG-500 (self collection) tubes twice (sample 1: prior to starting FMT#1, sample 2: after FMT#1, prior to starting conditioning chemotherapy). will be collected using Zymo DNA/RNA shield tubes enabling self-collection by participants and easy transport in the registered mail.

See Table 4a,b for biospecimen collection schedule.

Blood will be collected at the following timepoints (+/- 2 days):

**Table 4a Tab4:** Blood collection schedule

Before starting FMT#1	Day of chemotherapy infusion	Day 0 (HSCT)	Post HSCT period	Day of discharge	Day ~ 35*
X	X	X	A maximum of 5x weekly aligning with routine blood draws	X	X

* Aligning with relevant clinic follow up appointment

Stool will be collected at the following time points (+/-2 day depending on the bowel habits of the participant):

**Table 4b Tab5:** Stool collection schedule

Before starting FMT#1	Day of chemotherapy infusion	Day 0 (HSCT)	Post HSCT period	Start of FMT #2	End of FMT#2	Day ~ 35*
X	X	X	A maximum of 5x weekly while and in-patient*	X	X	X

* If out-patient, participant will self-collect

### Follow up

At 1 month after the last FMT capsule is taken, participants will complete a final set of assessments to determine symptom burden and to identify any adverse events that may be related to the FMT. ESAS-r-CS will be completed to determine symptom burden. Adverse events will be reviewed and categorised using NCI CTCAE v5.0. Assessments will be performed over the phone by a member of the study team.

### Data management

All data collected from participants in the HSCT-BIOME trial wil be de-identified using their unique Study ID. Data will be collected directly from participants in the form of hard copy Case Report Forms (CRFs) which will be securely stored in a locked filing cabinet that is only accessible to study staff.

Identifiable data (consent forms, pathology reports, etc.) will be de-identified and filed with the study documents. All participant files will be reconciled and stored along with all study materials – both hard copy and electronic – consistent with ICH GCP and applicable regulations regarding the retention and disposal of participant records.

All study data (de-identified) will be scanned into electronic PDFs and stored on a secure, regularly backed-up web-based platform (LabAchives) before being entered into REDCap (Research Electronic Data Capture); a secure web-based application designed to support data capture for research studies [18]. All web-based information transmissions in REDCap are protected via Secure Sockets Layer (SSL) encryption (data entry, survey submission, web browsing, etc.).

### Data analyses and synthesis

All qualitative data will be presented as descriptive data (e.g. participant demographics) and compared between groups using a Chi squared test. Study endpoints will be analysed as follows:

Effectiveness: Proportion of participants that meet the primary endpoint. This will be compared between the two arms using a Chi squared test.Safety: The incidence of all treatment-related AEs and SAEs will be compared between the two groups using a Chi squared test.Adherence: The proportion of participants that take all capsules. This will be compared between the two arms using a Chi squared test.Exploratory microbiota analyses: Uptake of the FMT will be determined by bacterial genome sequencing performed on faecal samples collected from participants.

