### Study setting

Royal Adelaide Hospital, Adelaide, Australia.St Vincent’s Hospital, Sydney, Australia.

Further sites may be added once the trial has commenced. These will remain restricted to Australia.

All samples will be processed locally, but stored at the South Australian Health and Medical Research Institute or at BiomeBank (Adelaide, South Australia).

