### Participants and study recruitment

The HSCT-BIOME trial will recruit eligible participants scheduled for conditioning chemotherapy prior to autologous HSCT for a haematological malignancy (Table 1).

This is a pilot study aiming to recruit N: 51 participants. This will adequately power the study to detect a 40% absolute reduction (80–40%) in the proportion of participants that meet the primary outcome of the study (alpha: 0.05, beta: 0.2, power 80%).

Potentially eligible participants will be identified at multidisciplinary team meetings (MDTs), hospital admissions and outpatient clinics The study will be introduced to the participant by their clinician, and provided with the PICF and the study will be introduced to the participant by their clinician. Between stem cell mobilisation and providing consent for their HSCT, participants will be given the PICF and consent will be collected at the same time as consenting for HSCT.

Once consented to the study, the participant is assigned a Study ID which will be used to identify all study material.

**Table 1 Tab1:** Inclusion and exclusion criteria

Inclusion	Exclusion
1. Age ≥ 18 years	1. Pre-existing gastrointestinal disease including Crohn’s disease, ulcerative colitis
2. Diagnosis of multiple myeloma, lymphoma or another haematological malignancy to be treated with auto-HSCT	2. Unable to swallow capsules
3. Scheduled to receive conditioning chemotherapy (+/- TBI) prior to auto- HSCT	3. Pregnancy
4. Able to provide written informed consent and follow all clinical trial related procedures (translator to be provided for people of culturally and linguistically diverse (CALD) backgrounds)	4. Nut allergy or anaphylactic food allergy
	5. Uncontrolled vomiting or oral mucositis that may impact swallowing (determined by participant) **
	6. Fever (body temp > 37.8oC) **

**Eligibility criteria to be reviewed before post-HSCT FMT intervention

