#### Randomisation

The trial statistician will be responsible for generating the randomisation schedule (stratified for site and conditioning regimen). This will assign a randomisation code to either placebo or the FMT. Participants will be randomised at a ratio of 2:1 (intervention to placebo).

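### Randomisation is stratified by site and conditioning regimen, but the named primary test uses neither; if they are prognostic, the test is conservative and forgoes power

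*Protocol article*

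**What the plan says.** In the protocol article, the Randomisation section makes the trial statistician responsible for "generating the randomisation schedule (stratified for site and conditioning regimen"). It also states: "Participants will be randomised at a ratio of 2:1 (intervention to placebo").

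Data analyses and synthesis fixes the primary (effectiveness) comparison: "Proportion of participants that meet the primary endpoint. This will be compared between the two arms using a Chi squared test". It names no stratum, covariate or adjusted model, and no other section does so for this endpoint.

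Participants and study recruitment gives the size: "This is a pilot study aiming to recruit N: 51 participants". The target is to "detect a 40% absolute reduction (80–40%) in the proportion of participants that meet the primary outcome of the study", with "alpha: 0.05, beta: 0.2, power 80"%. Study setting names two sites and adds: "Further sites may be added once the trial has commenced".

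The article does not give the number of conditioning regimens, the stratum sizes, the block size, or any diarrhoea risk by site or regimen.

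**The concern.** Stratified allocation forces the arms towards balance on site and regimen. If either factor predicts severe diarrhoea, the design has removed between-stratum variation from the difference between arms. The plain chi-squared variance still contains it. The test is then conservative, and a stratified test would detect the same effect more often.

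This is a mismatch between two stated methods. It is not a detail left to a statistical analysis plan, because a plan that used a stratified primary test would depart from the test the article names. What is at stake is precision in a trial of 51 that has little to spare: its calculated power is just over 80%, and that figure contains no allowance for dropout.

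**Working it through.** **1. The plan's own sample size.** Inputs from Participants and study recruitment and from Randomisation: 80% vs 40%, alpha 0.05, power 80%, 2:1. Two-sided testing without continuity correction is assumed, because the article states neither. The pooled rate is p̄ = (0.8 + 2 × 0.4)/3 = 0.5333.

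n(placebo) = [1.96 × √(p̄(1−p̄) × 1.5) + 0.8416 × √(0.8×0.2 + 0.4×0.6/2)]² / 0.4²
= [1.1976 + 0.4453]² / 0.16 = 16.87, rounded up to 17.

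The total is 17 + 34 = **51**, as stated. Power at 17/34 is Φ[(0.4×√17 − 1.1976)/√0.28] = Φ(0.854) = **80.3%**. The sample size and the plain test therefore agree with each other. (A one-sided test with continuity correction also gives 51.)

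**2. Size of the plain test with no stratum effect.** Exact enumeration at 17 vs 34, for common risks of 0.40 to 0.80, gives a size of 0.048 to 0.059. That is not conservative.

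**3. Why prognostic strata change this.** Under the null, the plain test uses p̄(1−p̄). With full balance the true variance is only the within-stratum part, Σwₛpₛ(1−pₛ). With R the ratio of the second to the first, the approximate size is 2[1 − Φ(1.96/√R)]. The inputs are assumed: four strata with shares 35/25/25/15%.

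| Null risks by stratum | p̄(1−p̄) | Within | R | Approx. size |
|---|---|---|---|---|
| Mild: 0.62/0.57/0.50/0.45 | 0.2473 | 0.2434 | 0.984 | 4.8% |
| Moderate: 0.75/0.60/0.42/0.30 | 0.2461 | 0.2180 | 0.886 | 3.7% |
| Strong: 0.90/0.70/0.25/0.12 | 0.2450 | 0.1467 | 0.599 | 1.1% |

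**4. Simulation of the same case.** 20,000 runs, N = 51, the same four strata and null risks, permuted blocks of 6 at 2:1. Control risks for power: none 0.80 throughout; mild 0.85/0.82/0.75/0.75; moderate 0.92/0.85/0.70/0.62; strong 0.97/0.92/0.60/0.50. The overall effect is about 80% vs 40%. Monte Carlo SE is about 0.0015 for size and 0.003 for power.

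| Strata | Size, plain | Size, CMH | Power, plain | Power, CMH | CMH minus plain |
|---|---|---|---|---|---|
| None | 5.3% | 4.9% | 81.5% | 79.8% | −1.7 |
| Mild | 5.2% | 4.9% | 81.7% | 80.8% | −0.9 |
| Moderate | 4.1% | 4.9% | 82.9% | 84.8% | +1.9 |
| Strong | 1.6% | 4.9% | 84.3% | 91.9% | +7.6 |

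The simulated sizes sit a little above the approximation in step 3. That is expected, because the test is discrete and balance within strata is incomplete.

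**5. Other assumed strata.**
- Four strata, blocks of three, 8,000 runs. With null risks of 30% vs 80% across regimens, size is 2.3% plain vs 4.0% CMH. Power is 84.2% vs 89.3% (strong), 82.2% vs 84.0% (moderate) and 81.4% vs 80.0% (none).
- Two sites by two regimens. Size is 2.5% vs 4.7% under strong strata, and 4.9% vs 5.0% under a 25-point regimen gap. Power is 81% vs 88% (strong), 84% vs 85% (moderate) and 82% vs 80% (none).
- Four sites by three regimens, uncollapsed, no prognostic effect. Power is 81% vs 77% in one run, and 81–82% vs 75–77% in another. With a 14-point regimen gap it is 82% vs 77–79%.

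From CMH, the gain is thus 5 to 8 points (strong) or 1 to 2 (moderate). The loss is 1 to 2 points with few non-prognostic strata, and about 4 to 5 with many sparse ones.

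**The case against.** The best defence is that the plain test does what the plan claims for it. It matches the sample size calculation, and its power is at least 81% in every simulated scenario. Any error from ignoring the strata is towards conservatism. The article also gives no reason for stratifying: site is often a stratum for logistical reasons, and nothing shows that regimen moves the diarrhoea risk. The large effects above need very wide gaps, such as 30% vs 80%. A CMH test is not free either, since 51 participants spread over many strata can take its power below 80%.

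All of this stands, and it limits the point. A reader might infer that the stated test is invalid or raises the false-positive risk, that the planned power is lost, or that the sponsor stratified because it expects regimen to drive toxicity. The article supports none of these. A reader might also count the absence of a stated estimate and interval as a fault; a condensed article may leave that to the analysis plan.

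What the defence does not remove is that the published primary test sets aside factors that the published design uses. The trade also favours using them if strata are kept few: 1 to 2 points at risk, against up to 8 gained.

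**Conclusion.** The point holds in conditional form. The named primary test ignores both stratification factors. If they are strongly prognostic, its size is about 2% against a nominal 5%, and 5 to 8 points of power are forgone relative to CMH. If they are moderately prognostic, 1 to 2 points are forgone. If they are weakly prognostic or not at all, the plain test is at about nominal size and CMH offers no gain.

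It would be too strong to say that the test is conservative as it stands, or that power falls short. Without prognostic strata its exact size is 0.048 to 0.059, and what is forgone is a possible gain above a target that is met. Every stratum risk, share and block size used here is an assumption, so the direction is firmer than the size. This is a worthwhile correction, not a threat to the validity of the trial.

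**What to change.** Replace the primary-test sentence in Data analyses and synthesis with a Cochran-Mantel-Haenszel test using the randomisation strata, reported with a Mantel-Haenszel risk difference and 95% CI. Keep the plain chi-squared as a sensitivity analysis.

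Add a rule for sparse strata: pool small sites and rare regimens, or stratify by regimen alone if cells are still too small. Base it on stratum counts only, not on outcomes or arms. Fix it before any Stage 2 unblinding; the Blinding section unblinds investigators each time a participant reaches the primary endpoint, so information on outcome by arm builds up during the trial. The rule matters more if sites are added.

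The cost is a few sentences and no extra participants. In power it is about 1 to 2 points if a few strata turn out not to be prognostic, and about 4 to 5 if many sparse strata are left uncollapsed, which the rule is there to prevent.

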### Blinding

Stage 1: No blinding (open label).

Stage 2: This will be a double-blind trial. If a participant reaches the primary endpoint (development of severe diarrhoea within 3 weeks post HSCT) investigators will be unblinded. If the participant is receiving placebo, they will be given a rescue course of open-label FMT (30–36 capsules taken over 5–6 days, i.e. 6 capsules, 3 BD). This innovative design enables the evaluation of the therapeutic efficacy of FMT (i.e. impact of FMT on diarrhoea) without compromising the validity of the trial’s primary objective.

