#### Stage 1 – Safety run in

Safety: Incidence of adverse events (AEs) assessed using the NCI CTCAE v5.0 (when in patient) with focus on treatment emergent adverse events, i.e. those identified to be related to the IP. AEs will be assessed from the time of starting the first course of FMT until 1 month after completion of the second FMT course. These will be assessed daily if the participant is admitted, and weekly when discharged. When an out-patient, assessments will be performed weekly by a member of the study team (phone call to participants). The Safety Monitoring Committee will be responsible for assigning AEs to either the HSCT treatment or IP. If the AE is deemed as probably or definitely related to the IP, they will be defined as a TE-AE.

Adherence/feasibility: Adherence will be defined by the proportion of participants that complete full course of FMT defined by the number of returned (unused) capsules and from participants’ diaries. The IP will be deemed feasible if participants take at least 75% of each course (pre- and post-HSCT).

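### The two-group test of treatment-related adverse events has no rule for rescue FMT, so harms of rescue given to placebo participants count in the placebo group and shrink the FMT-placebo difference

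*Protocol article*

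**What the plan says.** Four statements in the protocol article have to be read together.

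- **Rescue (Blinding).** Investigators are unblinded when a participant reaches the primary endpoint, which must occur within 3 weeks of HSCT. "If the participant is receiving placebo, they will be given a rescue course of open-label FMT", consisting of 30–36 capsules over 5–6 days.
- **Collection window (Stage 1 – Safety run in; Exploratory outcomes; Follow up).** "AEs will be assessed from the time of starting the first course of FMT until 1 month after completion of the second FMT course". For Stage 2, "Safety and adherence will continue to be assessed as per Stage 1". The Follow up section adds: "At 1 month after the last FMT capsule is taken, participants will complete a final set of assessments", in part "to identify any adverse events that may be related to the FMT".
- **Definition (Stage 1 – Safety run in).** "If the AE is deemed as probably or definitely related to the IP, they will be defined as a TE-AE". Nothing separates randomised product from rescue product.
- **Analysis (Data analyses and synthesis).** "The incidence of all treatment-related AEs and SAEs will be compared between the two groups using a Chi squared test".

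The Blinding section says rescue leaves the primary objective valid. It makes no such statement about safety.

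**The concern.** Each rule is reasonable alone. Together they mean that the placebo group in the safety test is, for many of its members, placebo followed by a course of the product under test. If FMT causes related events, rescue raises the placebo-group incidence and the observed excess shrinks. For a safety comparison this is the unfavourable direction, because it moves the result toward no difference.

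Safety is one of the main questions. The Study aims list FMT treatment-emergent event rates as one of three aims, and the Discussion expects the trial to clarify whether post-HSCT capsules can be given safely to immunocompromised patients. A null chi-squared result read as FMT versus placebo would give reassurance that the comparison cannot support.

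**Working it through.** **1. Group sizes and the plan's own figure.** Inputs from Participants and study recruitment and from Randomisation: N = 51, allocation 2:1, 80% versus 40%, alpha 0.05, power 80%. Two-sided pooled-variance formula without continuity correction, with pooled proportion (0.8 + 2 × 0.4)/3 = 0.533:

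n(placebo) = [1.96 × √(1.5 × 0.533 × 0.467) + 0.842 × √(0.16 + 0.24/2)]² / 0.4² = 16.9, rounded up to 17.

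With 34 on FMT the total is 51, which reproduces the stated size.

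**2. Does rescue fall inside the collection window?** Course 2 starts after HSCT and lasts 14 days (Table 2). Where it is taken, the window runs to at least day 14 + about 30 = day 44. The latest rescue trigger is day 21, so at least 44 − 21 = 23 days of collection follow it. A 5–6 day rescue started at once ends by about day 27. In addition, the only FMT capsules a rescued placebo participant takes are the rescue capsules, so a final review timed from the last FMT capsule follows rescue by a month.

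**3. How many placebo participants are exposed?** Expected number = 17 × endpoint rate × uptake. Write u for the share rescued. If rescue raises the incidence of treatment-related events among rescued participants by r, placebo-group incidence rises by u × r. The table takes r = 10 points.

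| Endpoint rate × uptake | u | Expected of 17 (binomial 5th–95th percentile) | Points lost from the FMT excess |
|---|---|---|---|
| 80% × 1 (planned rate, full uptake) | 0.8 | 13.6 (11–16) | 8 |
| 80% × 0.75, or 60% × 1 | 0.6 | 10.2 (7–13) | 6 |
| 40% × 1 | 0.4 | 6.8 (4–10) | 4 |
| 40% × 0.75 | 0.3 | 5.1 (2–8) | 3 |

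Only the first row uses the planned rate with every eligible participant rescued; the other rows are assumptions. Uptake could fall short if the vomiting, mucositis and fever review in Table 1 also applies to rescue.

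**4. How much of a true excess survives?** Let q be the background placebo risk, f the FMT risk, e = 1 − (1 − f)/(1 − q) the FMT-attributable risk, and k the attributable risk of rescue relative to randomised FMT. Observed placebo risk = 1 − (1 − q)(1 − u·k·e), so the share of the true difference retained is 1 − u·k.

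- k = 1: 20% retained at u = 0.8, 40% at 0.6, 60% at 0.4.
- k = 0.5: 60%, 70% and 80%.

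Illustration with assumed rates and u = 0.8. A true 5% versus 30% appears as 25% versus 30% if k = 1, or 15% versus 30% if k = 0.5. At k = 1 the exact power of the uncorrected chi-squared test at 17 versus 34 falls from 0.57 to 0.055. For a true 10% versus 40%, seen as 34% versus 40%, it falls from 0.625 to 0.07.

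For small excesses the test is weak even without rescue: power 0.048 for 0% versus 10% and 0.241 for 0% versus 15%. There the damage is to the estimate and how it is labelled.

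**5. Would stopping the count at the endpoint be enough?** Not with crude incidence. At the planned rates, follow-up would end early for 0.8 × 17 = 13.6 placebo and 0.4 × 34 = 13.6 FMT participants. If the endpoint falls at fraction s of the window, placebo keeps 1 − 0.8(1 − s) and FMT keeps 1 − 0.4(1 − s): 44% and 72% at s = 0.3, 68% and 84% at s = 0.6 (s assumed). Now suppose no FMT effect, a constant hazard and an assumed 30% full-window risk:

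- s = 0.3: risk to the cut = 1 − 0.7^0.3 = 10.15%. Placebo 0.8 × 10.15% + 0.2 × 30% = 14.1%; FMT 0.4 × 10.15% + 0.6 × 30% = 22.1%.
- s = 0.6: risk to the cut = 1 − 0.7^0.6 = 19.3%. Placebo 21.4%; FMT 25.7%.

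Unequal follow-up alone produces a spurious FMT excess of 4 to 8 points.

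**The case against.** The strongest reply is that handling of events after a treatment switch usually belongs in the statistical analysis plan, and that a journal article gives safety one sentence. The article does not say outright that post-rescue events are counted under placebo; that is inferred from the window and the reference to two groups. This stands as a caveat, since an unseen plan could set a cut-off. It does not remove the point: the article does state the rescue, the window and the comparison, and followed as written they give a diluted contrast.

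A reader might go further in three ways that the documents do not support.

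- *The trial will understate the harm of FMT.* Only the between-group difference is diluted. The FMT-arm rate, which is what the Study aims ask for, is untouched by placebo rescue. The Safety Monitoring Committee also assigns each event to HSCT or to the product, so rescue-related events can be identified.
- *The net bias must be toward no difference.* That holds for rescue alone. Investigators are unblinded at the endpoint in both arms, and the committee judging relatedness includes site investigators. If known FMT exposure makes attribution more likely in the FMT arm, that part moves the other way.
- *The test loses nearly all its power.* That needs assumed event rates and rescue as harmful as randomised FMT. Two randomised courses total 72 capsules against 30–36 for rescue, so equal risk is nearer an upper bound.

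**Conclusion.** The concern holds for the between-group safety comparison. With no rescue rule, treatment-related events caused by rescue FMT fall in the placebo group on the plain reading, and rescue biases the difference toward no difference whenever FMT causes such events. The article powers the trial on an 80% placebo rate ("This will adequately power the study to detect a 40% absolute reduction", from 80% to 40%). At that rate with full uptake, about 13.6 of 17 placebo participants become FMT-exposed, and the observed excess loses 8 points for each 10 points that rescue adds among them. Exposure falls to about 5 of 17 under the lowest assumed rate and uptake.

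The direction for the rescue component follows from the stated rules. The size does not, because no adverse-event rates are given. The primary endpoint is reached before rescue and is not affected. The point should be fixed before the safety data are analysed; it does not threaten the design.

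**What to change.** 1. Keep the full-window as-randomised comparison, label it *FMT versus placebo with FMT rescue*, and state that it is not to be read as FMT versus placebo safety.
2. Use the date of the first rescue capsule to tabulate placebo-arm events after it separately, as FMT-exposed.
3. If a pre-rescue FMT versus placebo contrast is given, run it in both arms from the first capsule to the earlier of the primary endpoint or the end of the collection window. Use exposure-adjusted rates or time to first event, not crude incidence, because placebo follow-up ends earlier.
4. Beside it, report FMT-arm events after the endpoint and during course 2 in full, so that post-HSCT harms are not lost.

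The cost is protocol or analysis-plan wording, one date and some extra tables. Sample size, design and primary analysis do not change. The pre-rescue contrast will have wider intervals, and its follow-up ends informatively at severe diarrhoea, which exposure adjustment does not cure. It should be read with items 1, 2 and 4, not alone.
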